## Data Analysis

A pre-post analysis will be conducted to compare practice patterns and performance of the intervention versus the control group (statistically a difference in difference fixed effects analysis). This analysis uses the CPV® scores as the outcome variable and includes basic bivariate analysis to determine group differences followed by a difference-in-difference, fixed effects multi-variate regression analysis, controlling for provider characteristics, to identify significant differences across the two groups.

|             |                                                                                                                                                |                       |
|-------------|------------------------------------------------------------------------------------------------------------------------------------------------|-----------------------|
|             | Clinical Study Protocol                                                                                                                 |                       |
|             | Title: Measuring the Clinical Utility of Aegis’s Chronic Disease Management Test among VillageMD Providers: A CPV® Randomized Controlled Trial |                       |
| Supersedes: | Document Number:                                                                                                                               |                       |
|             | Effective Date:                                                                                                                                | Page: 12 of 25 |

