## 2.1 Study Instruments

There are two data collection instruments: 1) the provider questionnaire; and 2) the CPV® simulated patient cases.

The online provider questionnaire consists of 10-15 questions to better understand provider demographics, training and practice environment. It will be administered once, upon enrollment into the study.

The CPV® cases will be designed to simulate typical patients with chronic cardiometabolic conditions and polypharmacy. In each case, providers will care for the simulated patient by indicating their preferred course of action to work- up, assess, and manage these patients. Providers will complete the cases in random order to cancel out any learning effects (which are known to be small), and only the intervention group will receive CDMT results at the appropriate point in each round 2 CPV® case whether they select it or not. All told, nine cases

|             |                                                                                                                                                |                       |
|-------------|------------------------------------------------------------------------------------------------------------------------------------------------|-----------------------|
|             | Clinical Study Protocol                                                                                                                 |                       |
|             | Title: Measuring the Clinical Utility of Aegis's Chronic Disease Management Test among VillageMD Providers: A CPV® Randomized Controlled Trial |                       |
| Supersedes: | Document Number:                                                                                                                               |                       |
|             | Effective Date:                                                                                                                                | Page: 16 of 25 |

will be developed, and any given provider will randomly be assigned to two rounds of three cases. Intervention will occur between the two rounds.

CPV® vignettes will be designed based on a 3 x 3 matrix of chronic cardiometabolic diseases and common drivers for non-adherence and potential drug-drug interactions.

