##### *Longitudinal Data Analysis*

Primary Outcome Variables:

- Baseline variation in care among providers using standard of care tools, as measured by CPV® patient simulations
- In the intervention group, change in the overall and the diagnostic and treatment evidence-based quality scores and reductions in variation when caring for the CPV® simulated patient with the introduction of CDMT testing.

|             |                                                                                                                                                |                       |
|-------------|------------------------------------------------------------------------------------------------------------------------------------------------|-----------------------|
|             | Clinical Study Protocol                                                                                                                 |                       |
|             | Title: Measuring the Clinical Utility of Aegis’s Chronic Disease Management Test among VillageMD Providers: A CPV® Randomized Controlled Trial |                       |
| Supersedes: | Document Number:                                                                                                                               |                       |
|             | Effective Date:                                                                                                                                | Page: 22 of 25 |

- Changes in evidence-based management medication decisions (treatment) based on patient’s CDMT result.
- Distinguishing between medication non-adherence, DDI, and full compliance with suboptimal medication treatment (inadequate dosing vs. ineffective medication).
- Change in cost of chronic disease-related care. (This cost is modeled in part by measuring differential rates of work up/interventions/levels of care selected by each arm and multiplying by average Medicare reimbursement rates for these workups/interventions/ levels of care, and/or by modeling the incidence of expected complications and calculating associated costs per above).
- Difference in the above cost and clinical quality metrics and cost measures by three different use case types.

Secondary Outcome Variables:

- Calculation of the change in the expected cost and clinical quality metrics for each type simulated patient case (use case).

Main Explanatory Variable:

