- Intervention status (exposure to intervention)

We will control for all potential confounders, including:

- Age
- Gender
- Years in practice
- Practice location
- Type of location (urban/suburban vs. rural)
- Weekly hours in clinical practice
- Number of providers in practice
- Avg. type of coverage of patients (Medicare, Medicaid, commercial, etc.)
- Participation in care quality incentive programs
- Percentage of patients that have chronic cardiometabolic disease

We will model CPV® scores as a continuous outcome variable in a multiple linear regression model, which controls for all potential confounders listed above.

Our regression model is as follows, where CPV® is the score for each provider and INTERV indicates intervention group and CASE indicates the order in which the provider took the case (first, second, third, fourth).

|             |                                                                                                                                                |                       |
|-------------|------------------------------------------------------------------------------------------------------------------------------------------------|-----------------------|
|             | Clinical Study Protocol                                                                                                                 |                       |
|             | Title: Measuring the Clinical Utility of Aegis’s Chronic Disease Management Test among VillageMD Providers: A CPV® Randomized Controlled Trial |                       |
| Supersedes: | Document Number:                                                                                                                               |                       |
|             | Effective Date:                                                                                                                                | Page: 23 of 25 |

$$Y_{it} = \text{CPV}^{\circledR} \text{ score of provider } i, \text{ at time } t$$

$$Y_{it} \sim \text{Normal}(\mu_{ijt}, \sigma^2)$$

$$\mu_{ijt} = \beta_0 + \beta_1 \text{CASE} + \beta_2 \text{INTERV} + \beta_3 \text{CASE} \times \text{INTERV} + \text{provider-practice variables}$$

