For binary outcome variables, we will use a logistic regression model. Our regression is as follows, where INTERV indicates intervention group and TIME indicates time period (by week). For outcomes with a Poisson distribution, the distributional assumption would be changed from

Bernoulli to Poisson and the link would be changed from logit to log. Otherwise, the basic modeling and analysis strategy will remain the same.

$$Y_{it} = \text{appropriate therapy } t, \text{ provider } i$$

$$p_{it} = \text{probability of an outcome for time } t, \text{ provider } i$$

$$\text{logit}(E[Y_{it}]) = \beta_0 + \beta_1 \text{CASE} + \beta_2 \text{INTERV} + \beta_3 \text{TIME} \times \text{INTERV} + \text{provider-practice variables}$$

For count outcome variables we will use log linear regression (i.e., using a log link in the analysis). Cluster re-sampled bootstrapping will be used to check model distributional assumptions.

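### The written score model has no within-provider term although each provider gives six scores, and it has no parameter for the variation outcome

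*Protocol*

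**What the plan says.** Section 2.1 of the protocol says that "any given provider will randomly be assigned to two rounds of three cases", so each completing provider contributes six scores. Section 8.b, Longitudinal Data Analysis, sets out the analysis of these scores: "We will model CPV® scores as a continuous outcome variable in a multiple linear regression model, which controls for all potential confounders listed above". The equation beneath has a normal outcome with one σ², terms for CASE, INTERV and CASE × INTERV, and provider-practice variables. CASE "indicates the order in which the provider took the case (first, second, third, fourth"), a list that stops at four of the six cases. The outcome carries indices i and t, while its mean carries i, j and t; j is not defined.

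The same section applies this strategy to binary outcomes (logit link) and count outcomes (log link), again with no provider term. It adds: "Cluster re-sampled bootstrapping will be used to check model distributional assumptions".

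The synopsis, under Data Analysis, describes a difference-in-difference, "fixed effects multi-variate regression analysis, controlling for provider characteristics".

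The primary outcome list in Section 8.b includes "reductions in variation when caring for the CPV® simulated patient with the introduction of CDMT testing", and the hypotheses in Section 8.a expect less practice variation in the intervention group.

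**The concern.** Six scores from one provider will normally be correlated. An ordinary regression with one residual variance treats them as independent, so its standard errors are wrong whenever that correlation is positive. The direction depends on the contrast. A within-provider change gets too large a standard error and loses power. A between-arm comparison that pools several scores per provider gets too small a standard error and produces too many false positives.

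Two statements might repair this, but neither does so as written. The bootstrap is not named as the source of intervals or p-values. The fixed effects of the synopsis do not appear in the equation. If they mean provider effects, INTERV and every provider characteristic that is constant over time drop out, although both places ask for provider characteristics and the equation includes INTERV. The protocol therefore permits several analyses of the same data that give different p-values.

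A separate gap concerns variation. It is part of a primary outcome, but the only written model for scores has a single σ² and no parameter that measures a change in variation. Section 8.b names no other analysis for it.

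**Working it through.** **Inputs from the protocol.** 166 providers recruited, 83 per arm, 10% attrition, 75 per arm expected (synopsis, Sample Size); three scores in each of two rounds (Section 2.1). The attrition figure reproduces: 83 × 0.9 = 74.7, or about 75.

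**Assumptions.** The protocol states no ICC, SD, effect size, alpha or power. I take exchangeable ICC of 0.2 / 0.3 / 0.5, total variance 1, two-sided alpha 0.05, and a reference power of 80%. Every completer has six scores, because Section 4.c withdraws providers who do not complete three cases per round. Covariates are left out.

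**1. Treatment contrast (CASE × INTERV, CASE taken as round), n = 75 per arm.**
- Independence variance: 4/(3n) = 4/225, SE 0.133.
- True variance: 4(1 − ICC)/(3n), SE 0.119 / 0.112 / 0.094.
- Model SE over true SE: 1/√(1 − ICC) = 1.118 / 1.195 / 1.414, an overstatement of 12% / 20% / 41%.
- Type I error: 2[1 − Φ(1.96/√(1 − ICC))] = 2.8% / 1.9% / 0.6%.
- Power when the correct test has 80%: Φ(1.96 + 0.842 − 1.96/√(1 − ICC)) = 73% / 68% / 51%.
- The SE ratio is the same, to rounding, when CASE is coded as linear order 1 to 6.

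**2. Arm comparison within one round, three scores per provider.**
- Design effect: 1 + 2·ICC = 1.4 / 1.6 / 2.0.
- Model SE over true SE: 1/√(1 + 2·ICC) = 0.85 / 0.79 / 0.71, an understatement of 15% / 21% / 29%.
- Type I error: 2[1 − Φ(1.96/√(1 + 2·ICC))] = 9.8% / 12.1% / 16.6%.

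**3. INTERV coefficient.** With CASE coded as round, this is the round 1 arm comparison and step 2 applies. With CASE as linear order, the SE ratio is 0.98 / 0.98 / 0.96 and type I error is about 5% to 6%. With CASE categorical, the coefficient compares one score per provider (the first case), and type I error is 5%.

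**4. Providers who differ in response.** Let the response to the test vary between intervention providers with variance τ², in units of total variance. The true variance of the interaction becomes 4(1 − ICC)/(3n) + τ²/n, and the model variance is about (1 + τ²/4)·4/(3n). These are equal at τ² = 2·ICC, which is 0.4 / 0.6 / 1.0. Above that value the treatment test becomes anti-conservative.

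**5. Simulation check.** In 2,000 trials with CASE as round, at ICC 0.3 and 0.5, ordinary regression rejected a true null for the interaction in 2.3% and 0.4%, and for INTERV in 12.0% and 17.1%. Provider-clustered standard errors brought the interaction back to about 5.4% and 5.3%.

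These figures are for the linear score model. The logistic and count models omit the same term, but the percentages should not be carried over to them.

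**The case against.** The strongest defence is that the treatment claim is protected. Under exchangeable correlation the test that carries it errs on the safe side. If the synopsis means provider fixed effects, CASE × INTERV survives, and its standard error is right under that correlation. This stands as far as it goes, so a reader should not infer that the plan inflates false-positive efficacy claims; only a wide spread in provider response would do that. But the equation contains no such effects, and they could not be added while INTERV and the time-constant covariates stay.

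A reader might also attach the 10% to 17% type I error to the INTERV coefficient. The protocol defines CASE as order, and under that coding the coefficient is close to nominal. The inflated figures belong to comparisons that pool scores, such as the bivariate group comparisons in the synopsis, if these are run per case.

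A third tempting reading is that one σ² assumes the variation outcome away. The documents do not support it. The equation is a model for mean scores and does not claim to analyse variation. Nor does the common variance distort the treatment test: reducing the intervention arm's round 2 variance to 75%, 50% or 25%, with no correlation, leaves the SE ratio at 1.00 in the balanced design. What stands is that no stated analysis answers that outcome.

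A separate analysis plan might supply both missing pieces. The protocol nevertheless writes out a specific model, and that model and its description in the synopsis do not agree.

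**Conclusion.** The point holds. The protocol fixes a score model that ignores clustering by provider, extends it to binary and count outcomes, and describes it differently in the synopsis. For the treatment test the likely cost is power: from 80% to about 73%, 68% or 51% at ICC 0.2, 0.3 or 0.5, with no stated effect size or margin to absorb the loss. For pooled one-round arm comparisons the cost is type I error of about 10%, 12% or 17%. All sizes rest on the assumed ICC and on exchangeable correlation. The direction for the treatment test can reverse if responses differ widely between providers. The missing analysis of variation is a specification gap for a primary outcome and does not bias the treatment test.

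**What to change.** - In the Section 8.b models, add a provider random intercept (a generalised linear mixed model for binary and count outcomes) with provider-clustered standard errors. Alternatively, state that the provider-level cluster bootstrap supplies the intervals and p-values. The clustered errors or the bootstrap matter because a random intercept alone does not cover differing responses.
- Define index j, and make the synopsis and Section 8.b name the same model.
- State an arm-by-round comparison of variance for the variation outcome, for example by letting the residual variance differ by arm and round and reporting the ratio.
- Optional: adjust for the round 1 score. This gains precision. It does not correct an error, since the unadjusted difference-in-difference is unbiased under randomisation.

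The cost is wording in the synopsis and Section 8.b, carried into any analysis plan. Standard software is enough, and no further data are needed. It should be settled before outcome data are seen.

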## Study Design

The study is a prospective randomized cohort two-arm trial with six steps:

- 1) Enrollment: The study will enroll an estimated 166 practicing primary care providers, who practice at VillageMD clinics. An eligibility screener will be used to screen for eligibility (attached as Appendix A).
- 2) Provider survey: Once providers are enrolled in the study, they will be asked to complete an item questionnaire describing their practice, professional background and confidence in treating patients with cardiometabolic conditions.
- 3) Randomization: The 166 VillageMD providers will be randomized into two equally- sized arms: control group and intervention group.
- 4) CPVs® (First Round): Providers in both groups will complete three CPV® patient vignettes. Cases will be identical across the intervention and control arms. Cases are interactive and are presented on an online platform that is accessible via unique weblinks and any internet-connected computer.
- 5) Intervention education: For the intervention group, providers will receive educational materials describing the clinical validation and use cases of the Chronic Disease Management Test. The education materials are an orientation to the test, its use, the results directed to the participants that will adopt the CDMT (e.g., introduction slide deck, fact sheet, and/or case studies)
- 6) CPVs® (Second Round): All participating providers will then be asked to complete three additional CPV® patient simulations. The cases are again given to the doctors in a random order.

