### 3.1 Outcome Measures

- Baseline levels of variation in the work-up, recognition, and management of medication non-adherence and/or DDI in patients with more than one chronic cardiometabolic conditions and associated polypharmacy among all participants.
- Pre- and post-difference in the overall and the work-up, recognition and management quality scores between control providers using standard of care diagnostic tools and intervention providers with access to CDMT results.
- Differences in evidence-based decisions, particularly prescribing decisions, made by intervention providers and control providers, while controlling for provider and practice characteristics, between rounds 1 and 2.
- Distinguishing between medication non-adherence, DDI, and full compliance with suboptimal medication treatment (inadequate dosing vs. ineffective medication).
- Difference in expected cost of care between control and intervention providers (Cost will be calculated by measuring differential rates of medical interventions/levels of care selected by each arm, and multiplying by Medicare reimbursement rates for these interventions, and/or by modeling the incidence of expected complications and calculating associated costs per above).
- Difference in the above cost and clinical quality metrics and cost measures by three different use case types.

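### The only CPV-score regression written out has no round term, so its interaction is an arm difference in slope over case order, not the promised difference-in-differences

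*Protocol*

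**What the plan says.** The design is a two-round trial. In the Synopsis, Study Design, round 1 is "Providers in both groups will complete three CPV® patient vignettes", and for round 2 "All participating providers will then be asked to complete three additional CPV® patient simulations". Section 2.1 agrees: "any given provider will randomly be assigned to two rounds of three cases", and "Intervention will occur between the two rounds".

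The target of the analysis is also stated. The Synopsis, Data Analysis, describes a pre-post comparison of intervention with control, "statistically a difference in difference fixed effects analysis". Section 3.1 lists as an outcome "Pre- and post-difference in the overall and the work-up, recognition and management quality scores between control providers" and intervention providers.

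The model for CPV scores is in Section 8.b, Longitudinal Data Analysis. Its mean is an intercept, a CASE term, an INTERV term, a CASE x INTERV term and provider-practice variables, each of the first three with a single coefficient. The text defines the two variables: "INTERV indicates intervention group", and "CASE indicates the order in which the provider took the case (first, second, third, fourth" (the list ends there). There is no term for round and no provider effect.

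The logistic model that follows in the same section has CASE and INTERV as main effects, but its interaction is TIME x INTERV, with TIME counted in weeks. TIME has no main effect, and again nothing marks the round.

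**The concern.** The intervention acts as a step: nothing differs between arms in cases 1 to 3, and education plus test results apply in cases 4 to 6 of one arm. A difference-in-differences needs a variable that switches between the third and fourth case, and its product with arm is the effect. The written equation has no such variable. The nearest term, CASE x INTERV, measures how much faster scores rise per case in one arm than in the other. Read as the effect of the test, it would be wrong in size and unit. The definition of CASE also does not reach the fifth and sixth cases, which are two of the three post-intervention cases of each provider. An analyst following the section would have to choose a coding after the fact, and the codings give different coefficients.

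**Working it through.** **Inputs from the protocol.** Three cases in each of two rounds, so 3 + 3 = 6 per provider; intervention between the rounds; INTERV is arm; CASE is order, listed to four. The Synopsis sample size can be reproduced: 83 x 0.90 = 74.7, about 75 per arm, and 2 x 83 = 166. It gives no effect size, SD, alpha or power, so these are assumptions below, and effects are expressed as multiples of d.

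**Assumptions.** A pure step of size d in the intervention arm from case 4 on, no baseline arm difference, and CASE coded numerically 1 to 6, as the single coefficients imply.

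1. *What the interaction estimates.* Let t = 1,...,6 with mean 3.5, and s = 0, 0, 0, 1, 1, 1.
   - Sum of (t - 3.5)^2 = 17.5 (variance 17.5/6 = 2.917).
   - Sum of (t - 3.5)s = 0.5 + 1.5 + 2.5 = 4.5 (covariance 4.5/6 = 0.75).
   - Interaction coefficient = d x 4.5/17.5 = 0.257d per case.

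2. *Can it be rescaled?* Over the 3-case gap between round means it gives 3 x 0.257d = 0.771d. Over the 5 steps from first to last case it gives 1.286d. Neither returns d.

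3. *What INTERV becomes.* The average arm difference over six cases is 0.5d, so the fitted INTERV coefficient is 0.5d - 3.5 x 0.257d = -0.4d, although the true baseline difference is zero.

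4. *Numerical check with d = 10.* Least squares on noise-free data gives:

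| Model | INTERV | Interaction |
|---|---|---|
| CASE numeric 1 to 6, as written | -4.0 | 2.57 |
| POST (0 for cases 1-3, 1 for cases 4-6) | 0 | 10.0 |

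5. *Efficiency.* The slope and step contrasts both sum to zero within provider, so a constant provider effect cancels from each. Their squared correlation is 4.5^2/(17.5 x 1.5) = 20.25/26.25 = 0.771, and the correlation is 0.8783.

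6. *Illustrative power* (two-sided 0.05, exchangeable errors). Power = Phi((1.960 + z) x 0.8783 - 1.960).
   - 80%: (1.960 + 0.842) x 0.8783 - 1.960 = 0.501, power about 69%.
   - 90%: (1.960 + 1.282) x 0.8783 - 1.960 = 0.887, power about 81%.

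7. *CASE as a factor.* With six levels and d = 10, the interaction terms relative to case 1 are 0, 0, 0, 10, 10, 10. The mean over cases 4-6 minus the mean over cases 1-3 is 10.0, the difference-in-differences. This needs all six levels and that particular contrast. The section writes neither.

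**The case against.** The strongest reply is that the protocol states the right question twice, in the Synopsis and in Section 3.1. The equation would then be a careless rendering that a competent analyst would put right, for example with a six-level factor and a round contrast. It is true that the target is stated and that the factor coding could recover it. But the section writes single coefficients and four levels, so the equation contradicts the target; it is not a detail left open for the analysis plan.

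Section 8.b also names exposure to the intervention as the main explanatory variable, which might suggest that INTERV switches on only in round 2. The sentence that introduces the model defines it as group, however.

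Several stronger readings are tempting and are not supported:

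- *That the coding produces false positives.* With no intervention effect, randomisation makes the expected CASE x INTERV coefficient zero.
- *That cases 5 and 6 would be discarded.* Nothing says so, and Section 4 requires three completed cases per round to stay in the study. A listing slip is more plausible.
- *That CASE restarts in each round, leaving no time information.* A three-case round could not reach a fourth case.
- *That no categorical coding could give the effect.* Step 7 of the working shows that one can.
- *That this is the designated primary model and its interaction will be reported as the effect.* The protocol does not say either. It is simply the only model written out for CPV scores, and change in those scores is among the primary outcome variables.

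**Conclusion.** The point holds as a contradiction between the written equation and the protocol's own design and stated analysis. Under numeric coding 1 to 6 and a step after the third case, the interaction equals 0.257d per case instead of d. That result needs no assumption about variance, alpha or power. The 77% efficiency also needs exchangeable errors. The falls from 80% to about 69% and from 90% to about 81% further assume a two-sided 0.05 test and are illustrative, since the protocol gives no basis for power. The harm is a misparameterised estimate and lost power, with an unplanned choice of coding left to the analyst. It is not a bias of the test under no effect. The equation should be corrected before the data are analysed.

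**What to change.** In Section 8.b, Longitudinal Data Analysis, change the CPV-score model as follows:

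- Replace CASE in the main effect and the interaction by POST, equal to 0 for cases 1-3 and 1 for cases 4-6.
- Name the POST x INTERV coefficient as the effect estimate.
- Include a provider effect, as the fixed-effects wording in the Synopsis implies. If it is fixed, INTERV and covariates that are constant within provider are absorbed by it, and POST x INTERV remains estimable.
- Keep case order only as a covariate with a main effect common to both arms, and extend its list to the six cases taken.

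Make the same change in the logistic model, replacing the week-based interaction by POST x INTERV with a POST main effect.

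The cost is two equations and their variable definitions, carried into the statistical analysis plan if one exists. Round is already known for every case, so no further data are needed.

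### The logistic model for binary outcomes tests a per-week slope (TIME x INTERV, with no TIME main effect and no round term), which is not the round 1 to round 2 difference-in-difference the protocol promises

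*Protocol*

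**What the plan says.** Protocol Section 8.b (Longitudinal Data Analysis) states: "For binary outcome variables, we will use a logistic regression model". In plain notation the printed equation is logit(p) = b0 + b1 CASE + b2 INTERV + b3 TIME x INTERV + provider-practice variables, "where INTERV indicates intervention group and TIME indicates time period (by week"). The outcome named beside it is appropriate therapy. For Poisson outcomes only the distribution and the link change.

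CASE is not defined beside this equation. The definition given for the continuous score model is: "CASE indicates the order in which the provider took the case (first, second, third, fourth"). That model interacts CASE, not TIME, with INTERV and has main effects for both.

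The synopsis (Data Analysis) calls the intended comparison "statistically a difference in difference fixed effects analysis". Section 3.1 sets the contrast of evidence-based decisions between arms from round 1 to round 2. Section 2.1 fixes when exposure starts: "Intervention will occur between the two rounds".

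**The concern.** Exposure is a switch. An intervention provider is unexposed in all three round 1 cases and exposed in all three round 2 cases. The printed model has no term for that switch. It has a weekly slope, fitted in the intervention arm only, which also runs through the unexposed first round.

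Two things follow. First, b3 is a log odds ratio per week, so the same intervention effect gives a different b3 when providers work to a different schedule. Second, control providers can change only through CASE. A change common to both arms that CASE does not describe can be fitted only in the intervention arm, through b3, where it looks like an effect of the test. The outcome named for this model, appropriate therapy, belongs with the medication decisions that Section 8.b lists among its primary outcome variables.

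**Working it through.** **Inputs from the protocol.** 83 providers per arm with 10% attrition: 83 x 0.9 = 74.7, which reproduces the stated 75 per arm. Each provider takes two rounds of three cases, so six in all. The protocol gives no gap between rounds, entry pattern, baseline rate or within-provider correlation. These are assumed below.

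**Step 1: what b3 measures.** Let a provider do round 1 in week w1 and round 2 in week w2.
- Control change: b1 x (change in CASE).
- Intervention change: b1 x (change in CASE) + b3 x (w2 - w1).
- Difference-in-difference: b3 x (w2 - w1).

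So b3 is the effect divided by the gap. A log odds ratio of 1.0 gives 1.0 to 0.5 per week for gaps of 1 to 2 weeks, 0.33 to 0.17 for 3 to 6 weeks, and 0.125 to 0.083 for 8 to 12 weeks. Simulated mean values of b3 for the same effect, across several sets of assumed inputs, were 0.29 to 0.91, 0.16 to 0.20 and 0.08 to 0.09. The runs disagree at the shortest gap but all show the same dependence on schedule.

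**Step 2: why a shared step leaks into b3.** Take no intervention effect, a shared step s at round 2, CASE linear over orders 1 to 6, equal arms and the same gap for everyone. Use a linear approximation to the logit.
- Control arm: the sum of squares of CASE is 17.5, and its cross-product with the step is (0.5 + 1.5 + 2.5)s = 4.5s.
- Intervention arm: TIME x INTERV already fits the round difference, so only within-round variation in CASE remains. Its sum of squares is 2 + 2 = 4, and its cross-product is 0.
- Common slope: b1 = 4.5s / (17.5 + 4) = 0.209s.
- Mean case order differs by 5 - 2 = 3 between rounds, so CASE explains 3 x 0.209s = 0.628s. The remaining 0.372s goes to b3 x gap.

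For s = 0.8 and a 4-week gap, b3 = 0.372 x 0.8 / 4 = 0.074 per week with no true effect. Simulation of this setting (baseline logit -1, provider SD 0.7) gave 0.068.

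**Step 3: false-positive rates with no intervention effect** (75 per arm, six cases, nominal 5%).

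| Change common to both arms | CASE coding and schedule | Model as printed |
|---|---|---|
| None | linear, gap 3-6 weeks | 4-5% |
| Step 0.2 logit | linear, gap 3-6 weeks | about 6% |
| Step 0.5 | linear, gap 3-6 weeks | 8-11% |
| Step 1.0 | linear, gap 3-6 weeks | 20-26% |
| Step 0.8 | linear, gap 4 weeks for all | 21% |
| Step 0.8 | linear, gap 2-8 weeks, staggered start | 11% |
| Exactly linear in case order | linear | 5% |
| Any step up to 1.0 | six categories | 4-6% |
| Trend 0.15 per week | six categories, gap 2-8 weeks, staggered start | 41% |

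A model with a round term and round x INTERV gave 4 to 6% throughout.

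**Step 4: recovery of a real effect.** With a true round 2 log odds ratio of 0.8 and a shared step of 0.8, the printed model (CASE linear) gave b3 = 0.25 with a 4-week gap for all, and 0.11 with variable gaps. The round x INTERV model gave 0.72 and 0.73, as expected when a within-provider 0.8 is averaged over providers.

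**Step 5: if CASE is a slip for TIME.** With TIME as the main effect, false positives return to about 5 to 7%. For a log odds ratio of 1.0, b3 still varies with the gap: 0.47, 0.18 and 0.09 per week for 1 to 2, 3 to 6 and 8 to 12 weeks. If TIME is calendar week and entry is staggered over an assumed 8 weeks, power was 57% against 93% for POST x INTERV in one run, and about 40 to 60% against 90 to 94% across the runs.

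**The case against.** The strongest reply is that the inflation is conditional. It needs a change shared by both arms that CASE leaves unexplained. The protocol describes learning effects as small and randomises case order, and controls receive neither education nor test results. A shared step of 1.0 logit is an odds ratio of 2.7 in untreated providers, and nothing in the document points to that. With a small step such as 0.2 the rate is about 6%. The coding of CASE is also open: the stated list of orders stops at the fourth of six cases, and six categories absorb a step completely. All of this stands, and it limits the size of the problem.

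A reader might infer that TIME in weeks is unrelated to exposure. That goes too far. Round 2 follows round 1 for every provider, so weeks counted from entry are correlated with exposure. The fair criticism is that weeks are a poor, schedule-dependent proxy. The protocol does not say whether weeks are counted from entry or by calendar.

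A drafting slip is plausible, since TIME is defined next to this equation and CASE is not. Step 5 shows that the slip reading cures the false positives but not the dependence on schedule. The slip would need correcting in any case.

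None of these replies makes b3 the round 1 to round 2 contrast.

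**Conclusion.** The equation is wrong as printed. Under each reading considered, b3 is a weekly slope whose size depends on the schedule, and it conflicts with the difference-in-difference in the synopsis and the round contrast in Section 3.1. This conclusion needs no assumed figures.

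The size of the harm does rest on assumptions. With 75 per arm, six cases, a 3 to 6 week gap and linear CASE, the false-positive rate is about 6%, 8 to 11% and 20 to 26% for shared steps of 0.2, 0.5 and 1.0 logit. The power loss rests on an invented 8-week stagger with calendar weeks.

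Two stronger readings are tempting. One is that Type I error is uncontrolled in general. The protocol does not support that, because the rate stays near 5% when there is no shared change or when CASE absorbs it. The other is that every diagnosis and prescribing result, or the main analysis, runs through this model. The protocol names only appropriate therapy beside the equation and analyses CPV scores with a separate linear model. The point covers the binary outcomes and, by the stated carry-over, the count outcomes.

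**What to change.** In Section 8.b, write the binary and count models as b0 + b1 POST + b2 INTERV + b3 POST x INTERV + provider-practice variables, where POST is 0 for round 1 cases and 1 for round 2 cases, with a logit or log link as appropriate. Name b3 as the intervention effect. Use provider-clustered standard errors, because each provider contributes six cases. Keep case order or case identity only as an adjustment, state how it is coded over all six cases, and drop TIME in weeks.

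The cost is one equation and a sentence of definition. No extra data are needed, since the round of each case is fixed by the design. The change should be made before outcomes are compared by arm.
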